Clinical guidelines are defined as “statements that include recommendations intended to optimize patient care. These statements are informed by a systematic review of evidence and an assessment of the benefits and costs of alternative care options” (21). Although guideline-based motor rehabilitation after stroke has been shown to be effective and important for those affected, physiotherapy has been found to deviate from the recommended practice (22–27). Possible reasons for non-adherence to guidelines in acute stroke rehabilitation may be related to healthcare professionals', patients', and healthcare institutions' characteristics, the complexity of some recommended therapies, or complexities in the guidelines themselves (28). In terms of the mobility of patients with stroke, Donnellan et al. noted that guidelines were not specific enough with regard to the performance of the recommended intervention (29). For the purposes of stroke rehabilitation, several guidelines have become available (30). Neurologists and physical therapists of the German Society of Neurorehabilitation (Deutsche Gesellschaft für Neurorehabilitation—DGNR) developed the interdisciplinary “rehabilitation of mobility after stroke (ReMoS)” guideline, which was first published in 2015 by the “Working Group of Scientific Medical Societies” (Arbeitsgemeinschaft Wissenschaftlicher Medizinischer Fachgesellschaften—AWMF) (31). According to the AWMF classification, the ReMoS guideline is considered an “S2e guideline” which implies that the guideline development process is based on a systematic literature search and a systematic selection and appraisal of the evidence. Considering the adverse events and the clinical applicability, the authors recommend therapy goal-directed interventions for improving walking ability, walking speed, walking distance, and the balance of individuals with sub-acute and chronic stroke (31). As the greatest potential for functional recovery in patients with stroke can be expected during the 1st months after disease onset (32), only recommendations for the sub-acute phase during the first 6 months are focused upon here (Supplementary Material 1).

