### Phase 4: Pilot Test of the Tailored Implementation Intervention

A controlled study design will aim to evaluate the effectiveness, appropriateness, acceptability, and feasibility of both the tailored implementation intervention and the implementation process in order to improve ReMoS guideline usage (65). The trial was registered on the German Clinical Trials Register with the number DRKS00019024. The reporting of this study will follow the “Standards for Reporting Implementation Studies (StaRI)” statement (66).

Routine practice shall be monitored in a single-center design in the “Elbland Rehabilitationsklinik” over a control period of 6 months. During this time, healthcare professionals shall not receive any instructions to change their habits or follow the ReMoS guideline recommendations any differently than they had before. Afterward, the implementation phase including the tailored implementation intervention shall be carried out (6 weeks). This will then be followed by a further monitoring period of 6 months. The implementation intervention shall be provided to all therapists involved in motor rehabilitation, regardless of whether they participate in the study.

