Healthcare professionals shall be eligible for participation if they are (1) ≥18 years old, (2) trained therapists providing motor rehabilitation, and (3) continuously employed during the study period. Patients will be eligible to participate if they are (1) ≥18 years old, (2) diagnosed primarily with stroke, and (3) having improvement in mobility as one of their activity-related rehabilitation goals. Reasons for exclusion include other diseases of organ systems that negatively impact on motor rehabilitation (e.g., other severe neurological or musculoskeletal conditions, acute renal or cardiac diseases and other pre-existing disorders that potentially reduce the rehabilitation potential). A study nurse shall screen patients for eligibility. Written informed consent shall be provided and approved before the start of the study for each participant. Primary implementation outcomes will be the German versions of the Acceptability of Intervention Measure (AIM), the Intervention Appropriateness Measure (IAM), the Feasibility of Intervention Measure (FIM), and ReMoS guideline adherence (healthcare professional level) (67). Secondarily recommended core-outcomes will be used for further evaluation at the patient level within 1 week after the start of rehabilitation, at the week of discharge, and 6 months after discharge for the health-related quality of life among people with stroke (PROMIS® Scale v1.2 - Global Health) (68–70). Recruitment and retention rate as well as compliance with the intervention protocol shall be evaluated at the study feasibility level (71). As the present study represents a pilot study for testing the feasibility, acceptability, applicability, and possible effectiveness of a targeted implementation intervention, the number of cases required to determine significant effects has not been determined beforehand. Data analysis as well as the blinding of patients, healthcare providers, and assessors will not be possible because of the controlled before-after experimental design and the active intervention measures. In order to reduce the risk of systematic bias, staff and patients will only be informed in detail about the content and objectives of the implementation study if this is explicitly requested (72). A between-group analysis will be used to evaluate pre-post changes to indicate whether the intervention is successful with regard to the primary healthcare professional and patient outcome.

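### The one-week window for the patient PROMIS baseline lets post-implementation baselines be taken under care that has already changed, which can dilute the between-period contrast of a secondary outcome

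*Protocol article*

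**What the plan says.** All of this stands in the protocol article under Phase 4: Pilot Test of the Tailored Implementation Intervention.

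- **Comparison.** "Routine practice shall be monitored in a single-center design in the “Elbland Rehabilitationsklinik” over a control period of 6 months". A 6-week implementation phase follows, then a second 6-month monitoring period.
- **Exposure.** "The implementation intervention shall be provided to all therapists involved in motor rehabilitation, regardless of whether they participate in the study".
- **Rank of the patient outcome.** The primary implementation outcomes are acceptability, appropriateness, feasibility and guideline adherence at the professional level. For patients, "Secondarily recommended core-outcomes will be used for further evaluation at the patient level", with PROMIS Global Health as the quality-of-life instrument.
- **Timing.** Patients are assessed "within 1 week after the start of rehabilitation, at the week of discharge, and 6 months after discharge". The schedule is stated once and applies to both periods.
- **Analysis.** "A between-group analysis will be used to evaluate pre-post changes to indicate whether the intervention is successful". The sentence goes on to include the patient outcome, but it does not say how the first assessment enters the analysis.

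No length of stay is given. The section also states that the number of cases needed for significant effects was not determined.

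**The concern.** A baseline should be measured before the exposure under study can affect it. Here the exposure is care delivered by therapists who have received the implementation intervention. By the second monitoring period that care is in place from a patient's first session. An assessment late in the permitted week is then a post-exposure value, while the matching control-period assessment follows only routine care.

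If such a baseline is subtracted or adjusted for, early benefit of the changed care is taken out of the contrast. The Conclusion says the project is meant to inform the power of future studies, so an attenuated patient-level difference would be carried into their planning. A baseline taken late cannot be recovered afterwards.

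**Working it through.** The plan gives no figure to reproduce on this point. The check is arithmetic on the two inpatient windows.

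**Inputs**
- Baseline on days 1 to 7 and second assessment in the last 7 days of the stay (Phase 4).
- Length of stay L: not in the document; assumed to be 21, 28 or 42 days.
- Also assumed: any between-period difference builds up linearly over the stay, and baselines are spread evenly over days 1 to 7 (mean day 4).

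**Step 1: what cancels.** Let r(t) be the recovery under routine care by day t, and d(t) the extra gain in the post-implementation period. With baseline on day b and second assessment on day e:
- control change = r(e) − r(b)
- post-implementation change = r(e) − r(b) + d(e) − d(b)
- difference = d(e) − d(b)

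With the same timing in both periods, ordinary recovery r cancels. Only d(b), the between-period difference present before baseline, is lost.

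**Step 2: size of the loss with a change score.** With linear d, the share of the full-stay difference lost is (b − 1)/(L − 1). The average is 3/(L − 1), and the largest value, with every baseline on day 7, is 6/(L − 1).

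| Assumed stay | Average loss | Largest loss |
|---|---|---|
| 21 days | 3/20 = 15% | 6/20 = 30% |
| 28 days | 3/27 = 11% | 6/27 = 22% |
| 42 days | 3/41 = 7% | 6/41 = 15% |

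Counting from day 0 gives averages of 3.5/L, that is 17%, 12.5% and 8%, so the convention matters little.

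**Step 3: other uses of the baseline.** If the baseline is a covariate with slope β, the amount removed is β × d(b), which does not exceed the change-score loss for β between 0 and 1. If discharge or 6-month values are compared between periods without the baseline, nothing is lost in this way.

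**Step 4: if timing differs between periods.** Then r(b) no longer cancels. A 3-day shift in the mean baseline day creates a false difference of about 3/L of the routine gain over the stay: 3/21 = 14%, 3/28 = 11%, 3/42 = 7%. These are shares of total recovery, not of the intervention effect. The shift itself is hypothetical.

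**Step 5: uneven intervals.** For a fixed stay, the shortest interval is (L − 6) − 7 = L − 13 days and the longest is L − 1. This gives 8 to 20, 15 to 27 and 29 to 41 days. If timing is independent and even over two 7-day windows, the interval has a standard deviation of √(2 × 7²/12) = 2.9 days. In both periods alike this is noise, not bias.

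**The case against.** The other side has a good deal on its side.

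- **Phase 4 does not test rehabilitation itself.** A reader might infer that a week of recovery goes missing from the effect. Step 1 shows otherwise: under a common schedule ordinary first-week recovery cancels. This stands, and it limits the point to dilution and noise.
- **No admission-to-discharge change score is defined.** The phrase about pre-post changes can equally mean before versus after implementation, and the modelling may be left to an analysis plan that is not shown. This stands, so the dilution is conditional on the baseline being used. It is still the only patient-level starting value named in a non-randomised comparison, so its use for change or case-mix adjustment is likely.
- **Early assessment is allowed.** The rule permits contamination and does not ensure it.
- **The Introduction does not show rapid first-week change.** A reader might take "As the greatest potential for functional recovery in patients with stroke can be expected during the 1st months after disease onset" as proof that days matter. It concerns functional recovery over months, not global quality of life over days.
- **Overlapping windows and drift are not shown.** The windows would overlap only for stays of 13 days or less (L − 6 ≤ 7). The document gives no evidence of such stays, and it lists the time points separately. Nothing in it suggests that assessment timing will change between periods.
- **A window has a practical reason.** Screening, consent and a mobility goal must come first, and recruitment and retention are themselves outcomes. This speaks against a hard short limit, but not against asking for the earliest feasible assessment.
- **Varying length of stay makes intervals uneven anyway.** True, and the fix does not cure that.

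**Conclusion.** The point holds in a limited form. The stated rule allows a post-exposure baseline in the post-implementation period. Where that baseline is used, the contrast between periods is diluted on average by about 15%, 11% or 7% for stays of 21, 28 or 42 days. Those figures rest on an assumed length of stay, linear build-up of the difference, even spread of baselines over the week, and a change score. The 30% figure for a 21-day stay also needs every baseline on the last permitted day and should not be taken as the expected loss.

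The documents do not support reading this as a demonstrated bias in the trial's result. Anything beyond dilution needs baseline timing to differ between periods. The wide discharge window costs precision only. The outcome is secondary, the pilot is unpowered, and the professional-level primary outcomes are untouched. The weakness is minor to moderate, and worth correcting because the correction is cheap and the lost information cannot be restored later.

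**What to change.** In the outcome paragraph of Phase 4, replace the open one-week window with a rule such as:

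*Patients complete the PROMIS Global Health at enrolment, before the first motor therapy session where possible and otherwise as early as feasible, at the latest one week after rehabilitation starts. The same rule applies in both monitoring periods. The dates of the first therapy session and of each assessment are recorded, and baseline timing is compared between periods.*

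Keeping the week as an outer limit means that no patient is lost to a tighter window. Late baselines are flagged, not excluded. The comparison of timing shows whether the situation in Step 4 has arisen.

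The cost is a few lines of wording and slightly tighter scheduling for the study nurse, who already screens patients. The change concerns the questionnaire only and does not touch when or how therapy is given.

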### Limitations

Neurorehabilitation services in Germany differ from others both in Europe and the world, which will probably impact on current practice, perceived barriers, and facilitators, the applicability of the implementation intervention, and the transferability of our results. The reasons underlying this might lie with the specifics of the respective rehabilitation systems and the comparatively low proportion of academically trained physiotherapists in Germany (98).

Despite the effort we expended on selecting the theoretical underpinnings, issues might still arise. Both the BCW and the TDF are validated and commonly used in implementation research, but to date, only the BCTTV1 has been translated into German (47). Here, a systematic procedure is used, but subjective and pragmatic decisions are still required. Further issues might also arise due to the design of the study components, since results rely in part on self-reported data and on limited blinding modalities and are subject to possible contamination.

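### The plan says the before-after design and the active intervention rule out a blinded data analysis; neither prevents a period-masked analysis of guideline adherence and PROMIS

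*Protocol article*

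**What the plan says.** The Phase 4 section of the protocol article describes a single-centre study with a 6-month control period, a 6-week implementation phase and then a second monitoring phase: "This will then be followed by a further monitoring period of 6 months". On who receives the intervention it says: "The implementation intervention shall be provided to all therapists involved in motor rehabilitation, regardless of whether they participate in the study".

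On blinding it says: "Data analysis as well as the blinding of patients, healthcare providers, and assessors will not be possible because of the controlled before-after experimental design". The sentence goes on to a second reason, so the full justification reads "because of the controlled before-after experimental design and the active intervention measures".

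The next sentence offers a partial safeguard: "staff and patients will only be informed in detail about the content and objectives of the implementation study if this is explicitly requested". The section then closes with the comparison itself: "A between-group analysis will be used to evaluate pre-post changes to indicate whether the intervention is successful", applied to the primary healthcare professional outcome and the patient outcome.

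The Limitations section concedes that "results rely in part on self-reported data and on limited blinding modalities and are subject to possible contamination".

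**The concern.** The blinding sentence has two faults. Its grammar makes data analysis itself one of the things that cannot be done, which cannot be meant. Once repaired, it gives two reasons why the analysis cannot be blinded, and neither is a reason.

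This is a rule that the article states and justifies, not a detail left to a fuller document. A later analysis plan that followed it would have no cause to include masking.

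At stake is the period comparison, which is meant to show whether the intervention succeeded. It is not randomised, and the Phase 3 section has the study team develop the intervention together with clinic stakeholders. If scoring, exclusions or the form of the comparison are settled while the period is visible, those decisions can lean towards the intervention, even without intent. The article's Conclusion says that the project will inform the power of future studies, so a distorted difference could carry over into the planning of the next trial.

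**Working it through.** No arithmetic applies. The article gives no sample size, significance level, effect size or standard deviation, and says that no case number was determined in advance. The check takes each party named in the blinding sentence and asks whether either stated reason prevents masking.

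**Inputs, all from the Phase 4 section unless noted**
- Comparison: pre-post, between groups, at one clinic.
- Recipients of the intervention: all motor-rehabilitation therapists; patients are not direct recipients.
- Primary outcomes: AIM, IAM, FIM and guideline adherence at the level of the healthcare professional.
- Patient outcome: PROMIS Global Health within 1 week of the start of rehabilitation, in the week of discharge and 6 months after discharge.
- Source of the Phase 4 adherence data: not stated. The Phase 1 survey measures adherence by self-report.

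**Step 1: which outcomes can be compared between periods.** AIM, IAM and FIM rate the delivered intervention. If they are collected only after implementation, their presence reveals the period, so they drop out. Adherence and PROMIS remain, two outcomes in all.

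**Step 2: data analysis.**
- *Reason 1, the before-after design.* The design yields two sets of observations, one per period. The period can be stored as A or B, and calendar dates can be replaced by days since admission or, for therapist-level records, dropped. Therapists must be employed throughout the study, so they may contribute to both periods. Paired data can be coded in the same way, which leaves the sign of the difference unknown to the analyst.
- *Reason 2, the active intervention.* It reveals the period to those who deliver or receive it. It reveals nothing to someone who holds only a recoded file of adherence and PROMIS values.

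Neither reason prevents a masked analysis.

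**Step 3: healthcare providers.** They receive the intervention and cannot be blinded. The statement is correct for them.

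**Step 4: assessors.** PROMIS is self-reported, so the patient is the assessor. If adherence is self-reported, the therapist is the assessor and cannot be blinded. An on-site assessor at a single clinic would know the calendar period. Only if adherence is rated from records can the rater be masked, by hiding dates and shuffling the order. Because the source is not stated, this holds only conditionally.

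**Step 5: patients.** The article already limits what patients are told, in order to reduce bias. That is partial masking in practice, and it is already in place.

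**Result.** The statement is right for therapists, partly right for assessors, already partly addressed for patients, and wrong for the data analysis.

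**The case against.** The strongest reply has four parts.

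*The point relies on repairing a garbled sentence.* True, but the literal reading contradicts the analysis announced later in the same section, and no other repair makes sense. The sentence needs correction either way.

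*Nobody is named as analyst, and the analytic choices belong in an analysis plan that is not shown.* This stands in part. The article does not say that those who develop the intervention will run the analysis, and fixing the choices in advance would remove much of the risk. The absence of those rules is therefore not part of this point. The wrong statement about what is possible remains.

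*The plan does not ignore bias.* This stands. It restricts information to staff and patients and discloses limited blinding, self-report and possible contamination. Disclosure does not, however, justify giving up a safeguard that is available.

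*It is a pilot, and masking may fail.* Group sizes or data content may reveal which code is which, and any adjustment for calendar time would need the dates. This stands as a limit on the benefit and keeps the point modest.

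A reader might go further and infer that assessors and patients could also be fully blinded, and that telling patients the objectives on request is itself a flaw. The article does not support that. The adherence source is not given, PROMIS is self-reported, and nothing suggests that requests would differ between periods. Withholding an answer until the last PROMIS assessment, 6 months after discharge, would be ethically debatable and no simple change.

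A reader might also infer that the design is the only reason given. The active intervention is the second.

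**Conclusion.** The concern holds for the data analysis only. Read in the one way that makes sense, the article wrongly says that the analysis cannot be blinded; guideline adherence and PROMIS Global Health can both be compared with the period masked. The impossibility holds for therapists, for AIM, IAM and FIM, and for self-reports at the point of collection.

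The direction and size of any resulting bias cannot be worked out from the document. The conclusion rests on two assumptions: that the sentence means blinding of the data analysis, and that adherence and PROMIS are the outcomes compared between periods, since AIM, IAM and FIM rate the intervention itself. This is a correction of wording plus an inexpensive protection, not a threat to the viability of the pilot.

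**What to change.** Rewrite the blinding sentence in the Phase 4 section so that it says the following:

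- Therapists cannot be blinded, nor can AIM, IAM, FIM or self-reports when they are collected.
- The adherence and PROMIS datasets go to the analyst with the period coded A/B and calendar dates replaced by days since admission (dropped where there is no admission date), and separate from the AIM, IAM and FIM data.
- The code is opened only after scoring, exclusions and the comparison are final.
- If adherence is rated from records, they are rated with dates masked and in random order.

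If the sponsor prefers an unmasked analysis, the article should give a reason that actually applies. The present approach of limiting detailed information to staff and patients can stay.

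The cost is the changed wording and a small recoding step by someone other than the analyst, with no extra visits. The final comparison has to wait until the data are complete. Masking will be imperfect if group sizes or data content reveal the period, and the report should say so.

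### Therapist-level guideline adherence is assigned a between-group analysis, although the design implies that the same therapists are measured in both periods; the change should be estimated within therapist.

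*Protocol article*

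**What the plan says.** All of this stands in the protocol article, section Phase 4: Pilot Test of the Tailored Implementation Intervention.

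- **Design.** "Routine practice shall be monitored in a single-center design in the “Elbland Rehabilitationsklinik” over a control period of 6 months". Six weeks of implementation come next. "This will then be followed by a further monitoring period of 6 months".
- **No parallel therapist group.** "The implementation intervention shall be provided to all therapists involved in motor rehabilitation, regardless of whether they participate in the study".
- **Who is enrolled.** Therapists must be adults, trained and providing motor rehabilitation, and "continuously employed during the study period".
- **Outcome.** One of the four primary implementation outcomes is "ReMoS guideline adherence (healthcare professional level"). The other three are the AIM, IAM and FIM ratings of the intervention.
- **Analysis.** "A between-group analysis will be used to evaluate pre-post changes to indicate whether the intervention is successful". The sentence goes on to cover the primary healthcare professional outcome and the patient outcome together.

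The section does not mention a paired, within-therapist or repeated-measures analysis. It states that no sample size was calculated, and it gives no number of therapists.

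**The concern.** For patients, who are presumably different people in the two periods, a between-group comparison fits. For therapists there are no two groups: one staff, all exposed to the intervention, is observed before and after. A between-group analysis, taken in its usual sense, treats the two sets of adherence values as independent samples and discards the correlation between a therapist's two values.

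Adherence is the primary outcome that lends itself to a before-after comparison, because AIM, IAM and FIM rate an intervention that does not exist in the control period. If r is positive, the confidence interval for the adherence change would be wider than the data warrant, and a real change could go unrecognised. The Conclusion of the article also says that the project is to inform the power of future studies. Without linkage by therapist, neither r nor the SD of the within-therapist change would be available for that purpose.

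**Working it through.** **Is it the same people?** Three statements are read together: a single centre with consecutive periods, the intervention for all therapists, and continuous employment as an entry criterion. A therapist present in only one period is not eligible, and no other clinic supplies a comparison group. Measurement of the same therapists twice is an inference, because no single sentence says it, but it is the reading that fits all three.

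**Is there a figure to reproduce?** No. The article gives no sample size, power, alpha, SD or correlation. Everything numerical below rests on assumptions.

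**Standard error.** Let n therapists be measured once per period, with equal SD s and within-therapist correlation r.

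- Correct variance of the mean change: 2s²(1-r)/n.
- Variance under independent groups: 2s²/n.
- Ratio of standard errors, independent to paired: 1/sqrt(1-r).

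This ratio does not depend on n or s.

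**Power.** Assumed: n = 15, a continuous normal outcome, a true shift of 0.6 SD, two-sided 5% level. The independent-groups SE is sqrt(2/15) = 0.365 SD at every r. Paired power comes from the noncentral t with 14 degrees of freedom and noncentrality 0.6/sqrt(2(1-r)/15). Power and type I error of the unpaired test come from simulating correlated pairs and applying the independent-samples t test (200,000 runs per value of r).

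| r | SE ratio | Correct SE (SD units) | Power, unpaired | Power, paired | True type I error of nominal 5% unpaired test |
|---|---|---|---|---|---|
| 0 | 1.00 | 0.365 | 35% | 33% | 5.0% |
| 0.2 | 1.12 | 0.327 | 34% | 40% | 3.0% |
| 0.4 | 1.29 | 0.283 | 32% | 51% | 1.4% |
| 0.6 | 1.58 | 0.231 | 29% | 68% | 0.4% |
| 0.8 | 2.24 | 0.163 | 26% | 93% | 0.02% |

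At r = 0 the paired test gains nothing and is marginally weaker, because it has fewer degrees of freedom. As r rises, the unpaired test loses power while the paired test gains it. The 35% is therefore the power of the unpaired test only if the values really were independent. It should not be set against paired power at higher r.

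**What carries over to a later study.** In the same simulation, with true variance 1, the pooled variance averaged 1.00 at every r. The between-therapist variance is thus estimated without bias whether or not the data are paired. The variance of the change, 2(1-r), falls from 2.0 at r = 0 to 0.4 at r = 0.8, and an unlinked analysis would not estimate it.

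**The case against.** The best defence is that the sentence is loose shorthand. It names no test, model, standard error or independence assumption, and it covers therapists and patients in one clause. Between-group could mean control period against post period, and the reference to pre-post changes is compatible with within-therapist change. An article commonly leaves the choice of model to the full protocol or analysis plan, which is not shown and may name a paired or mixed model. This limits the charge: a reader might infer that the plan contains a wrong standard error, and the document does not state one. It does not remove the point. The text is not silent: it names a class of analysis and applies it to the professional outcome. Nor can it mean comparing change scores between two therapist groups, because there is only one group.

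A second objection is that Phase 4 does not say how adherence is measured. The only definition is in Phase 1, where it is a group-level threshold of 80% of survey participants answering in the top two of four categories. If adherence came from treatment records, the formula for two values per therapist would not apply as given. That stands as a limit on the figures. The records would still be nested in the same therapists, so independence would still fail.

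A third objection is that this is a pilot, with no sample size set to detect effects, and that three of its four primary outcomes are unaffected. That stands too, and it lowers the priority. Still, the sentence makes this analysis the indicator of success, and lost precision matters most in a small sample.

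**Conclusion.** The point holds as a mismatch between the named analysis and the design for therapist-level adherence. It should be corrected, but it does not undermine the pilot. If the two periods were analysed as independent groups, the SE of the adherence change would be overstated by 12% at r = 0.2 and by 124% at r = 0.8, and not at all at r = 0. The power figures depend further on the assumed 15 therapists, 0.6 SD shift, continuous outcome and equal SDs, none of which the document gives.

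Three stronger conclusions are tempting and are not supported:

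- A reader might infer a risk of false positives. With positive r the opposite is true: the type I error falls below 5%, and the cost is lost precision.
- A reader might infer that a biased variance would pass into the planned randomised study. The between-therapist variance stays unbiased. What goes missing is r and the SD of change.
- A reader might infer that the confidence interval would be far too wide. That depends on r, which is unknown, and at r = 0.2 the difference is modest.

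**What to change.** In the Phase 4 analysis text, separate the two levels:

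- **Therapists.** State that ReMoS guideline adherence is compared within therapist, by a paired analysis or by a mixed model with period as fixed effect and a therapist random intercept, in a form suited to the scale of the outcome. Report the change with its 95% confidence interval, together with r and the SD of change for later planning.
- **Patients.** Keep the between-group comparison for the two patient cohorts.

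Assign each therapist a pseudonymous code from the start of the control period, so that the two periods can be linked. This is the time-critical part, because a paired analysis cannot be recovered from data collected without a link. The cost is a sentence or two of text and the code, with no additional measurements.
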